## Abstract

**Background:**

At an early stage, prostate cancer patients are often eligible for more than one treatment option, or may choose to defer curative treatment. Without a pre-existing superior option, a patient has to weigh his personal preferences against the risks and benefits of each alternative to select the most appropriate treatment. Given this context, in prostate cancer treatment decision-making, it is particularly suitable to follow the principles of shared decision-making (SDM), especially with the support of specific instruments like decision aids (DAs). Although several alternatives are available, present tools are not sufficiently compatible with routine clinical practice. To overcome existing barriers and to stimulate structural implementation of DAs and SDM in clinical practice, a web-based prostate cancer treatment DA was developed to fit clinical workflow. Following the structure of an existing DA, Dutch content was developed, and values clarification methods (VCMs) were added. The aim of this study is to investigate the effect of this DA on (shared) treatment choice and patient-reported outcomes.

**Methods/design:**

Nineteen Dutch hospitals are included in a pragmatic, cluster randomized controlled trial, with an intervention and a control arm. In the intervention group, the DA will be offered after diagnosis, and a summary of the patients’ preferences, which were identified with the DA, can be discussed by the patient and his clinician during later consultation. Patients in the control group will receive information and decisional support as usual. Results from both groups on decisional conflict, treatment choice and the experience with involvement in the decision-making process are compared. Patients are requested to fill in questionnaires after treatment decision-making but before treatment is started, and 6 and 12 months later. This will allow the development of treatment satisfaction, decisional regret, and quality of life to be monitored. Clinicians from both groups will evaluate their practice of information provision and decisional support.

**Discussion:**

This study will describe a web-based prostate cancer treatment DA with VCMs. The effect of this DA on the decision-making process and subsequent patient reported outcomes will be evaluated.

**Trial registration:**

The Netherlands National Trial Register: NTR4554, registration date 1 May 2014.

## Background

Prostate cancer (PrCa) is the most common malignancy in men in the western world, and in The Netherlands where more than 10,000 new prostate cancer patients are diagnosed each year [1]. Incidence is still growing due to earlier detection and an ageing population [2–4]. Based on demographic developments only, the incidence of prostate cancer in The Netherlands is expected to increase by 49 % between 2011 and 2030 [5].

For the treatment of localized (low and intermediate risk) prostate cancer, the most common curative treatment options include radical prostatectomy, external beam radiotherapy (EBRT), and brachytherapy. Each curative treatment option has a specific risk profile concerning the occurrence of treatment side effects (for example, impotence, incontinence, and bowel problems). Because curative treatment may not always be necessary as initial treatment for low-risk PrCa, active surveillance can be considered a valid option for avoiding or deferring the need for curative treatment. Active surveillance has some known psychosocial barriers like anxiety and uncertainty about disease progression, which can withhold patients from choosing this option, although active surveillance is increasingly applied in clinical practice [6, 7]. Clinical practice guidelines do not provide strong treatment recommendations given a lack of convincing evidence indicating superiority of any of the available options [8]. Choosing the most suitable treatment option therefore requires a patient to evaluate the treatment procedure, risk for side-effects and the chance of success for all available options. Combined with personal preferences and characteristics, identifying the best suitable treatment option is a difficult and stressful exercise for many patients [9, 10]. Further complicating factors are clinicians’ misinterpretation of patients’ preferences, (information) needs and the patient’s preferred role in the decision-making process [11–15]. Eventually, this may result in the clinician dominating in the treatment decision-making at the expense of the patients’ preferences. It is possible that expressing a dominant clinician view may contribute to observed regional variations in the management of prostate cancer [16–20].

During the past decade, several decision aids (DAs) have been developed with a special focus on prostate cancer care. Instruments range from information booklets to tailored web-based tools. The variety in the formats used may have contributed to the finding that effects on decisional outcomes have been inconsistent across randomized trials and that no effects on choice have been found [21, 22]. Systematic reviews further emphasize that many previous studies are at high risk of selection bias due to inadequate concealment or blinding of data collectors and outcomes assessors, and that more studies are needed to determine how DAs can be implemented best in clinical practice [21, 22].

Determining the effect of a DA intervention and finding optimal implementation methods are both aims of the current trial. A web-based prostate cancer treatment DA was developed to fit with Dutch clinical workflow. Based on the structure of an existing DA developed by Feldman-Stewart and colleagues [23, 24], Dutch content was written and values clarification methods (VCMs) were added. Adaptation of the DA was based on the International Patient Decision Aid Standards (IPDAS) [25].

## Methods/design

### Objectives and hypothesis

The main objective of this study is to investigate the impact of the DA on shared decision-making and treatment choice. It is hypothesized that DA usage will improve prostate cancer knowledge and satisfaction with information provision and therefore better prepare patients for clinical encounters and the following decision-making, which will result in lower levels of decisional conflict compared to standard care. Further, it is expected that better knowledge and less decisional conflict will also result in improved treatment satisfaction, less regret and, ultimately, improved health-related quality of life (HRQoL). In terms of actual choice, we expect less variation in selected treatments in the intervention group compared to the control group.

A secondary aim is to investigate optimal implementation, as previous studies have emphasized the need to gain more insight on this matter [21]. From the patient perspective, it is expected that some subgroups will experience more benefit from DA usage than others. To identify these groups, the moderating role of age, preferred role in the decision-making process, specific health skills (for example, health numeracy and literacy) and personality on the main outcomes will be investigated. Healthcare providers in the intervention group will be asked their opinion about implementation of the DA. This will be compared with an evaluation of information provision and decisional support as provided by healthcare providers in the control group.

### Study design

The design for this study is a two-armed pragmatic, cluster randomized controlled trial (CRCT). Clustering is performed at the hospital level, meaning that all included patients from a participating hospital are in the same study group. Participating hospitals can therefore provide the same type of care to all of their patients, making a CRCT less prone to contamination bias [26]. The study will be longitudinal, including patients immediately after prostate cancer diagnosis and following them for 12 months. Patient-reported outcomes from both arms will be compared. Involved healthcare professionals will be included in a survey-study to evaluate their opinion on working with the DA. A comparison will be made with procedures of usual care from the control group.

The description of this design follows the CONSORT recommendation for reporting on trials (www.consort-statement.org) with the extensions for pragmatic [27] and cluster [28] randomized trials.

### Randomization

Nineteen Dutch hospitals have been randomized to either ‘usual care’ (arm 1) or ‘usual care + DA’ (arm 2). With this so-called prerandomization, the conventional sequence of obtaining informed consent followed by randomization is reversed [29]. This prerandomization is needed because we make clinicians aware (when introducing the DA) of the principles of shared decision-making and the characteristics of the DA. This could affect the control group if they were recruited within the same hospital.

To prevent potential imbalance between the two arms that could arise from hospital characteristics (for example, hospital size and treatment profile), two strata were included in the randomization procedure. First, if cooperation between two hospital locations leads to overlap in medical staff or patients visiting both locations, there is a risk for contamination bias if these hospital locations are not in the same cluster. In our sample, four pairs of hospitals have this overlap in hospital staff or patient visits. To maintain variability in hospital characteristics within each cluster, only two pairs were allowed to enter the same cluster. The second criterion is related to hospital specific treatment variation. In The Netherlands, hospitals that perform robot-assisted radical prostatectomy indicate a significant larger proportion of their patients for surgery compared to other hospitals [4]. At the moment of randomization, three hospitals from our sample are known for having robotic surgery facilities to treat prostate cancer patients, and only two of these hospitals were allowed to join the same cluster.

Randomization was performed by a statistician not involved in the study and blind to the identity of the hospitals, using SPSS version 19.0 (Statistical Package for Social Sciences, Chicago, IL, USA). As a first step, the four paired hospitals were randomized (block size = 2). Next, the remaining 11 hospitals were also block randomized (block size = 6, with the last position unused). A set seed was chosen that fulfilled to the criteria that only two robot facilitated hospitals were allowed into the same cluster. The generated group order was then applied to a pre-existing list of participating hospitals, which was sorted in alphabetical order. As there is an uneven number of hospitals participating in this study, the largest cluster that was formed was identified as the intervention cluster.

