### Sample size calculation

The sample size for this study is determined by power analysis with decisional conflict as the primary measure. To be able to detect a clinically relevant minimum effect size [61] of .50, power is set at .80 and alpha at .05. With 19 hospitals (clusters) that agreed to participate, it is needed to estimate the intra-class coefficient (ICC). The ICC assesses the proportion of variance explained by clusters. Higher ICC values decrease effective sample size and statistical power. ICC ranges from 0 to .1 are considered common in medical literature [62]. A more specific review of ICC values in (cluster) RCTs with psychosocial measures is provided by Bell and McKenzie [63], which also included a cluster RCT evaluating a group support tool for prostate cancer patients [64]. The median estimated value for 82 longitudinal ICCs from 15 included studies was 0.0007, and the range found for decisional conflict was between 0 and 0.02. Given the considerable variability in ICCs that is found in literature, ICC for the current trial is set conservative at 0.01.

The attrition rate is set at 25 % to compensate for non-response to the questionnaires. This rate is comparable to studies in similar populations and following the same methods as this study does [65, 66]. Calculations show that a design with 19 clusters of 20 patients (380 patients in total) achieves a power of .8. Taking into account a 25 % attrition rate between the first and third questionnaire, the total sample size (rounded) will be set at 475 patients. This results in a recruitment of 25 patients per hospital.

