### Statistical analysis

All analyses will be conducted using SPSS version 19.0 (Statistical Package for Social Sciences, Chicago, IL, USA). A 0.05-significance level will be adopted in all statistical tests.

We will perform a descriptive statistical analysis of organizational (hospitals) and socio-demographic (patients) characteristics in order to assure the comparability of the intervention and control groups. Baseline measures and changes in outcome variables over the study period for each study arm will be presented as means (± SD).

The main outcome decisional conflict is measured at T1 and will be compared between both groups (intervention and control). Multilevel modelling will be carried to take the hierarchical structure of the data into account by specifying random effects at both hospital and patient level. The least square mean proportions will be estimated and compared to assess the effect of the DA on decisional conflict.

The secondary outcomes will also be compared between both groups using multilevel modelling. Some of the secondary measures consist of repeated measures (for example, HRQoL and decisional regret) and will be treated according the appropriate mixed-model approach; that is, repeated measures anova/ancova will be used for outcomes with two time points (decisional regret, treatment satisfaction), and a random coefficient approach will be used for outcomes with three time points (HRQoL) [67]. Observed variation in treatment choice during the trial period will be compared between groups and at level of the individual hospital. For this second comparison, each hospital’s particular historical treatment variation profile (2008 to 2012) will be obtained from the Netherlands Cancer Registry.

Potentially confounding variables (for example, personality, health skills, and age) will be explored for their impact on the primary and secondary outcomes. Missing data and drop-outs will be described.

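### Four overlapping hospital pairs appear to have been allocated as pairs, giving 15 randomised units, but the sizing and the multilevel model use 19 hospitals; the effect on the primary analysis is small

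*Protocol article*

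**What the plan says.** All places are in the protocol article.

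- **Randomization, opening:** "Nineteen Dutch hospitals have been randomized to either" usual care or usual care plus the decision aid.
- **Randomization, overlap:** "In our sample, four pairs of hospitals have this overlap in hospital staff or patient visits". For hospital locations of this kind, "there is a risk for contamination bias if these hospital locations are not in the same cluster". In this section the word cluster means a trial arm.
- **Randomization, restriction:** of the four pairs, "only two pairs were allowed to enter the same cluster".
- **Randomization, sequence:** "As a first step, the four paired hospitals were randomized (block size = 2"), and then "Next, the remaining 11 hospitals were also block randomized (block size = 6, with the last position unused").
- **Sample size calculation:** "With 19 hospitals (clusters) that agreed to participate". Here a cluster is a hospital, and the design is 19 clusters of 20 patients at an ICC of 0.01.
- **Statistical analysis:** the primary outcome is compared by multilevel modelling "by specifying random effects at both hospital and patient level". Secondary outcomes are also compared by multilevel modelling.
- **Discussion:** the institution is defended as the unit of analysis.

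No section mentions a pair level or 15 units.

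**The concern.** In a cluster randomised trial, the independent replicates for the arm comparison are the units that were allocated independently. Two hospitals that share staff or patients, and that receive one joint allocation, are not two independent replicates. Because both always fall in the same arm, any positive correlation between them adds to the variance of that arm's mean. A model with a random effect for hospital, and nothing above it, leaves that term out. The standard error of the arm effect is then too small and the degrees of freedom for the between-unit comparison too many.

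The protocol itself supplies the reason to expect correlation. It considers the overlap strong enough to contaminate the comparison if a pair were split. In the Discussion it also rejects the clinician as unit of analysis, partly because nurses who assist several clinicians could contaminate the data. The same argument applies one level up, to hospitals with overlapping staff or patients. At stake are the confidence interval and p-value for decisional conflict, and for the secondary outcomes analysed with the same levels.

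**Working it through.** **Counting the units.** Four pairs are 8 hospitals, and 19 - 8 = 11 singles, which matches the 11 in the Randomization section. Two pairs go to each arm. Two blocks of six with the last position unused split the singles 6 and 5.

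- Hospitals: 2×2 + 6 = 10 against 2×2 + 5 = 9, total 19.
- Allocated units: 2 + 6 = 8 against 2 + 5 = 7, total 15.
- Between-unit degrees of freedom: 19 - 2 = 17 (t = 2.110) against 15 - 2 = 13 (t = 2.160).

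**The plan's own figure.** Inputs from the Sample size calculation: effect 0.50 SD, alpha 0.05 (two-sided assumed), ICC 0.01, 19 hospitals of 20. The design effect is 1 + 19×0.01 = 1.19, so each hospital has effective size 20/1.19 = 16.807. SE = √(1/168.07 + 1/151.26) = 0.1121. Power is 0.994 by the normal approximation, or 0.987 with t on 17 df. The stated 0.80 does not reproduce from these inputs. That is a separate matter, but it shows that the design has room to spare at the stated effect.

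**Fifteen units, full sharing.** Assume that patients in the two hospitals of a pair are as alike as patients within one hospital (an upper bound). A pair is then one unit of 40. With weights m/(1 + (m - 1)×ICC), at ICC 0.01:

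- Pair: 40/1.39 = 28.777. Single: 16.807.
- Arm totals: 2×28.777 + 6×16.807 = 158.39, and 2×28.777 + 5×16.807 = 141.59.
- SE = √(1/158.39 + 1/141.59) = 0.1157, and 0.1157/0.1121 = 1.032.

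The same formula at other ICCs, with power at 0.50 SD from the noncentral t on 17 and 13 df:

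| ICC | SE, 19 hospitals | SE, 15 units | Ratio | Power, 19 | Power, 15 |
|---|---|---|---|---|---|
| 0.01 | 0.1121 | 0.1157 | 1.03 | 98.7% | 97.9% |
| 0.02 | 0.1207 | 0.1269 | 1.05 | 97.4% | 95.3% |
| 0.10 | 0.1750 | 0.1924 | 1.10 | 76.8% | 67.1% |

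These SEs weight the units optimally. If every patient keeps equal weight, as under a hospital-only model with equal hospitals, the true SE exceeds the 19-hospital value by 3.5%, 6.0% and 13.7%, and power on 15 units is 97.8%, 95.0% and 64.3%.

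**Type I error when the pair level is left out.** Simulated trials with 10 against 9 hospitals of 20 patients, two pairs per arm and full sharing (200,000 trials per setting in the main runs):

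| ICC | t-test on hospital means, 17 df | Hospital-only REML random intercept |
|---|---|---|
| 0.01 | about 5.8% | 4.3-5.1% |
| 0.02 | about 6.4% | 5.4-6.1% |
| 0.05-0.10 | 7.7-8.8% | about 7.5-8.8% |

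The range in the last column reflects mainly the degrees of freedom: 17 throughout, or residual df whenever the hospital variance is estimated as zero. The random-intercept model does better at small ICCs because the variance estimate cannot go below zero, which makes the test conservative. With half the cluster effect shared, that model gives 4.7% at ICC 0.01 and 5.3% at 0.02.

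**The case against.** Several points on the other side stand.

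- **The planned model is not a t-test on hospital means.** At the protocol's own ICC of 0.01, the planned type of model shows essentially no inflation, even under full sharing.
- **The larger figures need larger ICCs.** The Sample size calculation cites 0 to 0.02 for decisional conflict. The value 0.10 is only the top of a general medical range.
- **The within-pair correlation is not given.** The overlap may be in staff or only in patient visits, and its extent is not described. With zero correlation the standard error would not change.
- **This is a condensed article.** It states no method for degrees of freedom, so 17 is what a hospital-level analysis implies and not something the plan declares.

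The wording on the paired hospitals is also loose. Taken alone, a block size of 2 could mean that each pair was split between arms. That would defeat the stated contamination reason, so allocation as pairs is the sound reading.

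What does not stand is that the matter can simply be left to a fuller document. The article itself fixes the cluster count and the model levels, and both differ from its own randomisation.

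A reader might go further and infer that the primary test is materially anti-conservative, that the trial is too small, or that treatment choice is affected more. The documents do not support these. The first two would need ICCs above the range cited for the primary outcome. For the third, the protocol gives no ICC for treatment choice, and no categorical outcome was examined here.

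**Conclusion.** The point holds, with small consequences for decisional conflict. The randomised unit, best read as 15 pairs or single hospitals, is missing from the stated model and from the sample-size count. If pair members are positively correlated, the standard error is understated. Under full sharing, the 15-unit standard error is about 3% larger at ICC 0.01, 5% at 0.02 and 10% at 0.10. Type I error of the planned kind of model is near 5% at 0.01 and about 5.5-6% at 0.02; it reaches 7.5-9% only at 0.05-0.10. The sample size is not threatened: power at 0.50 SD on 15 units is about 95% or more for ICC 0.01-0.02. These figures assume 20 analysed patients in each hospital, two pairs per arm and a two-sided test. Severity is minor to moderate.

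**What to change.** Define the cluster as the randomised unit: 15 units, made up of four hospital pairs and 11 single hospitals. Make that unit the top-level random intercept in the primary and secondary models, optionally with hospital nested within it, and use small-sample degrees of freedom based on 15 units. Settle this before outcome data are analysed, so that the clustering level cannot appear to have been chosen on the results.

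In the Randomization section, state plainly that each pair was allocated as one unit, and use separate words for arm and cluster. In the Sample size calculation, describe 15 units, four of them of double size.

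The cost is one grouping variable, slightly wider intervals and fewer degrees of freedom. No extra patients or data are needed.

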### Study population, inclusion criteria and exclusion criteria

The DA is developed for the initial treatment decision in early-stage prostate cancer. In order to be eligible to participate in this study, a subject must meet the following inclusion criteria:Patient is diagnosed with low or intermediate risk prostate cancer (EAU/ESTRO criteria) [30].Patient is eligible for at least two of following treatment options: active surveillance, radical prostatectomy, brachytherapy, external beam radiotherapy.Patient has access to a PC, laptop or tablet with an internet connection.

Exclusion criteria are:A combination of PSA ≥10 and Gleason = 7 (which defines high-risk prostate cancer).Cognitive impairment or being too ill at time of the study.Insufficient understanding of the Dutch language to complete questionnaires and understand the DA.

